## Abstract

**Introduction:**

Patients with severe dry eye disease (DED) often have limited treatment options with standard non-surgical management focused on the use of artificial tears for lubrication and anti-inflammatory drugs. However, artificial tears do not address the extraordinary complexity of human tears. Crudely, human tears with its vast constituents is essentially filtered blood. Blood and several blood-derived products including autologous serum, have been studied as tear substitutes. This study proposes to test the use of whole, fresh, autologous blood obtained from a finger prick for treatment of severe DED.

**Methods and analysis:**

The research team at the two participating sites will approach patients with severe DED for this study. Recruitment will take place over 12 months and we expect to recruit 60 patients in total. The primary outcome of this feasibility study is to estimate the proportion of eligible patients approached who consent to and comply with study procedures including treatment regimen and completion of required questionnaires. The secondary outcome measures, although not powered for in this feasibility, include corneal inflammation (assessed by the Oxford corneal staining guide), patient pain and symptoms scores (assessed by the Ocular Surface Disease Index Score), and objective signs of DED as indicated by visual acuity (assessed by Schirmer’s test, tear break-up time, lower and/or upper tear meniscus height measurement). Other secondary outcomes include patients’ quality of life (assessed using the validated EQ-5D-5L Questionnaire), cost to the National Health Service (NHS) and patient (assessed via use of NHS services and privately purchased over-the-counter treatment related to DED) and safety measure of pressure within the eye (assessed by the Intraocular Pressure (IOP) Score).

**Ethics and dissemination:**

This protocol and any subsequent amendments, along with any accompanying material provided to the participant in addition to any advertising material used in this trial have been approved by the East of England - Cambridgeshire and Hertfordshire Research Ethics Committee (REC reference: 17/EE/0508). Written approval from the committee was obtained and subsequently submitted to the respective Trust’s Research and Development (R&D) office with final NHS R&D approval obtained. Data obtained from this study will be published in a suitable peer-review journal and will also presented at international ophthalmic conferences including the American Academy of Ophthalmology, the Royal College of Ophthalmology Annual Congress, the Association for Research and Vision and Ophthalmology, and the European Society of Cataract and Refractive Surgery. Information will be provided to patient groups and charities such as the Sjogren’s Society and the Royal National Institute of Blind People. This will also be shared with the study participants as well as with relevant patient groups and charities.

**Trial registration number:**

NCT03395431; Pre-results.

Strengths and limitations of this StudyThis single-blind randomised control trial addresses a significant problem by investigating the use of whole, fresh, autologous blood obtained from a finger prick for treatment of severe dry eye disease.The study intervention is cheap, simple and with minimal risk of complication.The intervention will allow for the delivery of the beneficial components of tears including growth factors and proteins found in whole blood.Patients in the intervention arm may experience soreness in fingers that are repeatedly pricked and will be advised to use a different finger for each eye.

## Introduction

Dry eye disease (DED) is an umbrella term encompassing a range of ocular diseases estimated to affect 14% of all adults aged 48–91 years.^1^ If left untreated, DED can lead to severe reduction in the quality of life (QoL) of the patient. It can also cause loss of vision, pain in response to light, painful recurring stabbing sensations and the feeling of grit in the affected eye(s). Studies show that moderate-to-severe DED can be as disruptive to patient QoL as angina.^2 3^ Despite this, only less than 2% of all UK medical research funding is directed at diseases of the eye, leaving eye research critically underfunded.^4^ No curative agents for DED exist. The treatment of the disorder is essentially symptomatic with standard non-surgical treatment focused on the use of artificial tears for lubrication and anti-inflammatory drugs.

Anti-inflammatory agents used in DED include topical steroids and ciclosporine drops but these can cause side effects that limit their long-term use.^5^ Topical steroids can also cause cataracts and glaucoma, all of which further limit their use. Surgical options for DED include punctal occlusion to reduce tear drainage, punctal cauterisation (burning the drainage channel of tears and preventing their outflow) and partial suturing of the eyelids. However, these treatment options are associated with adverse effects and varying levels of patient tolerability. Overall, available conventional treatment options for DED often only alleviate symptoms, have limited effectiveness, and in most cases patients may fail to respond—although the exact rate of treatment failure is unavailable in the published literature.

The mainstay of non-surgical treatment for DED focuses on the use of artificial tears. These can be purchased over the counter and include brand name products such as Viscotears and Optrex.^6^ Human tears contain an extensive range of growth factors, immunoglobulins, enzymes, cytokines, vitamins and electrolytes and these have been shown in numerous studies to be essential for the maintenance and proliferation of corneal epithelial cells as well as for defence against infection.^7^ It is well known that artificial tears fail to account for the extraordinarily complex composition of the natural tear film. Also, many artificial tears contain preservatives that have been shown to adversely affect the cornea.^8^ Crudely, the human tear with its vast constituents is essentially filtered blood and as such is an obvious source for a ‘tear mimic’ containing all tear constituents. Blood and several blood-derived products including autologous serum (AS) have been studied as tear substitute candidates.

AS eye drops have been found to be beneficial in uncontrolled trials by improving the ocular surface and reducing symptoms.^9–11^ However, a Cochrane review concluded that there is inconsistency in evidence on its benefit.^12^ Obtaining AS requires frequent drawing of blood from the patient—a feature that excludes patients with anaemia or heart failure from using AS. Furthermore it also appears that 100% AS is more beneficial than 50% serum and requires larger volumes of blood and/or more frequent venesection.^10^ Patients using AS also require access to a fridge, as the product needs to be stored at low temperatures—a factor that is likely to be inconvenient for patients. In addition, AS is obtained by processing clotted blood at an initial cost of £1653.56 to the National Health Service (NHS), and subsequent 3-monthly costs of £1131.27 per patient.

The relatively high cost represents the biggest hurdle in the use of AS and is often the reason for delay or inaccessibility in its use as a treatment for DED. We propose that finger prick autologous blood (FAB) is a simpler, cost-effective and possibly more acceptable method for treating DED. For this reason, this study proposes to test the use of FAB in which blood obtained from a small finger prick is applied to the eye. Autologous fresh blood is already being used in the subconjunctiva to help heal leaking trabeculectomy blebs.^13–16^ It is also used to help attach limbal autografts in cases of pterygium,^17^ and in vitreoretinal macular hole surgery^18–21^ with no adverse effects reported. The FAB method can be used in patients who are awaiting conventional treatment for autologous blood.

### Rationale and risks/benefits

This study proposes to test the feasibility of the use of whole, fresh, autologous blood as a treatment for severe DED (detailed study protocol presented as online supplementary file). The blood can be obtained from a clean finger, pricked by the patient using a diabetic lancet and administered immediately to the eye. This allows the delivery of most of the aforementioned beneficial components of tears and additional growth factors and proteins, fresh and unprocessed, which can help heal the ocular surface. If validated, this may replace current AS practice and with its ease of use, vastly reduced cost and greater convenience may mean that it could be extended to other ocular surface diseases. The proposing team have completed an exploratory study on the use of FAB for persistent epithelial defects and severe DED and preliminary results indicate improvement with no adverse events (AEs) reported.^22^ The exploratory study included 16 patients with a diagnosis of severe-to-moderate dry eye syndrome and used the FAB method for treatment. The findings of the study demonstrated mean improvements in visual acuity, Oxford corneal staining grade, tear break-up time and DED questionnaire score. The response rate from participants was good with only a single patient who met the inclusion criteria not wishing to participate in the trial. Both the amount of staining (indicating inflammation and ocular surface damage) and their DED questionnaire scores (indicating severity of their symptoms and impact on QoL) showed mean improvement which reached statistical significance. A search of clinical databases (Medline, CINAHL and AMED) including ongoing trials on the UKCRN (UK Clinical Research Network) portfolio database and related websites (www.controlled-trials.com) did not identify any studies using FAB as a treatment for DED.

10.1136/bmjopen-2018-026770.supp1Supplementary data

## Primary and secondary objectives

The primary objective is to determine the feasibility of a definitive randomised controlled trial (RCT) to evaluate effectiveness of the use of fresh autologous blood (FAB) compared with conventional treatment for patients with severe dry eye syndrome. The primary outcome is the proportion of eligible patients approached who consent to and comply with study procedure including treatment regimen and completion of required questionnaires. The secondary objectives, although not powered for within this feasibility include: to estimate the effectiveness of the trial intervention and further explore the acceptability of the study design, and to explore the feasibility of collecting resource use and QoL data to inform the design of the health economics component of a future definitive trial. The secondary outcome measures, although not powered for within this feasibility, include corneal inflammation (assessed by the Oxford Corneal Staining Guide), patient pain and symptoms scores (assessed by the Ocular Surface Disease Index (OSDI) Score) and objective signs of DED as indicated by visual acuity (assessed by Schirmer’s test, tear break-up time, lower and/or upper tear meniscus height measurement). Other secondary outcomes include patients’ QoL (assessed using the validated EQ-5D-5L Questionnaire), cost to the NHS and patient (assessed via use of NHS services and privately purchased over-the-counter treatment related to dry eye disease) and safety measure of pressure within the eye (assessed by the Intraocular Pressure (IOP) Score).

## Method

### Study design

This is a single blind, two-arm feasibility RCT of FAB with conventional treatment versus conventional therapy alone for severe DED, including a qualitative process evaluation (figure 1 provides details of the study scheme). This trial is ongoing and open to recruitment at two participating sites: Bedford Hospital NHS Trust and Moorfields Eye Hospital London. Recruitment into the trial commenced in April 2018 and is due to finish by April 2019.

**Figure 1 F1:**
[figure not shown]
Study scheme. FAB, fresh autologous blood.

### Sample size

As this is a feasibility trial, there were no formal sample size calculations.^23^ The aim of the study is to recruit a sufficient number of patients to evaluate the acceptability and feasibility of the intervention. An outcome of this study will be to estimate parameters such as the SD for a sample size calculation of a subsequent full-scale trial. A sample of 52 patients (26 in each arm) is considered adequate for obtaining reliable sample size estimates.^24 25^ To allow for a conservative attrition rate of 10%, we aim to recruit 60 patients into the trial.

### Participant selection

#### Inclusion criteria

Patient age ≥18 years.Severe symptomatic DED diagnosed by: OSDI Score >33; or Oxford corneal staining grade ≥2; or Schirmer’s test without anaesthesia <5 mm at 5 min.Patients on artificial tears and/or lubricating drops/gel four times a day.Patient able to give consent.Patients able and willing to complete the QoL Questionnaires required for the study.

#### Exclusion criteria

Fear of needles.Unable or not willing to carry out repeat finger pricks.Patients with infected finger/s or systemic infection or on systemic antibiotics for infection.Patients with active ocular infection, active immunological corneal melt or recurrent corneal erosion.Pregnant or breastfeeding women.Previous use of FAB treatment (eg, from exploratory study).Systemic illness causing immune system deficiency.Graft versus host disease.Previous use of AS within 3 months.Diabetes.

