### Outcome assessment

The primary outcome measure is the proportion of eligible patients approached who consent to and comply with the trial protocol. This will be assessed by: number of eligible patients within the study population and recruitment time frame, percentage of eligible patients accepted for randomisation, patient compliance with trial protocol measured as per self-reported adherence to intervention and percentage of patients completing study. The secondary outcomes include reduction in corneal inflammation (assessed by the Oxford corneal staining guide), patient pain and symptoms scores (assessed by the OSDI Score) and improvement in objective signs of DED as indicated by visual acuity, Schirmer’s test, tear break-up time, lower and/or upper tear menisci height measurement. Other secondary end points include patients’ QoL (assessed using the EQ-5D-5L Questionnaire), cost to the NHS and patient (assessed via use of additional NHS services and privately purchased over-the-counter treatments related to DED) and safety measure of pressure within the eye (assessed by IOP Score).

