#### Screening procedures

Patients will have undergone the below procedures as per standard of care which will in turn feed in to the investigator for their review prior to approaching the potential participant.OSDI Score >33; orOxford corneal staining grade ≥2; orSchirmer’s test without anaesthesia <5 mm at 5 min.

The results from these will be reviewed by the investigator prior to approaching the potential participant.

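### Willingness to finger-prick and to complete questionnaires is part of eligibility, so the primary feasibility proportion, taken over eligible patients approached, is partly conditioned on what it should measure

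*Protocol article*

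**What the plan says.** The Outcome assessment section of the protocol article defines the primary outcome: "The primary outcome measure is the proportion of eligible patients approached who consent to and comply with the trial protocol". The Primary and secondary objectives section spells out what must be complied with. Patients must "consent to and comply with study procedure including treatment regimen and completion of required questionnaires". One listed component is the "percentage of eligible patients accepted for randomisation", which has the same eligible base.

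The eligibility lists already contain willingness. An inclusion criterion reads "Patients able and willing to complete the QoL Questionnaires required for the study". Two exclusion criteria read "Fear of needles" and "Unable or not willing to carry out repeat finger pricks".

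Under Screening procedures the article names three severity tests (OSDI, Oxford staining, Schirmer) and adds: "The results from these will be reviewed by the investigator prior to approaching the potential participant". It does not say when willingness is assessed, or how a patient who objects to the pricks after being approached is classified.

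**The concern.** The Sample size section says the study aims to "recruit a sufficient number of patients to evaluate the acceptability and feasibility of the intervention". For this intervention the obvious obstacle to acceptability is the finger prick, done four times a day. With eight weeks of treatment (implied by the 12-week visit falling 4 weeks post-treatment), that is 4 × 7 × 8 = 224 pricks for each treated eye.

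If refusing the pricks makes a patient ineligible, that refusal cannot lower the primary outcome. Refusing the questionnaires is treated the same way, although completing them is named as part of the outcome. There is an asymmetry too. A sore finger after entry is a listed reason for withdrawal and so counts against feasibility, while the same objection made before entry does not count. The qualitative interviews cover patients using the blood treatment and clinicians, so nothing in them is designed to recover the views of those who declined.

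At stake is what the headline proportion means. It would describe uptake among people already willing to do the main things asked of them, yet it would be read as the acceptability of the approach in severe dry eye disease.

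**Working it through.** **The plan's own figure.** The Sample size section inflates 52 patients for 10% attrition: 52/0.9 = 57.8, so 58. The stated target of 60 is this figure with a small margin. The concern does not depend on it, but 60 and 52 supply reference values below.

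**Definitions**
- C = approached patients who consent.
- c = share of consenters who comply.
- r = approached patients who decline for reasons outside the eligibility list (randomisation, visits and so on).
- u = approached patients who meet the clinical criteria but are ruled out for unwillingness (pricks, needle fear given as the reason, questionnaires).

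**Formulas**
- Proportion as literally defined: C·c/(C + r).
- Proportion counting unwillingness as refusal: C·c/(C + r + u).
- Ratio of the first to the second: (C + r + u)/(C + r). This does not involve c, equals 1 when u = 0, and exceeds 1 for any u > 0.

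**Inputs.** From the article: C = 60 (recruitment target). Assumed: c = 52/60 = 86.7%, borrowing the ratio of the article's two sample sizes. Also assumed: r and u, for which the article gives no value. The exploratory study had 16 patients and one refusal among those meeting its inclusion criteria. Scaled to 60 entrants that is 60/16 = 3.75, so r = 4 is taken as a low case, with 20 and 40 as higher ones. The numerator is 60 × 52/60 = 52 throughout.

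| r (assumed) | As defined (all u) | u = 10 | u = 20 | u = 40 |
|---|---|---|---|---|
| 4 | 52/64 = 81.3% | 52/74 = 70.3% | 52/84 = 61.9% | 52/104 = 50.0% |
| 20 | 52/80 = 65.0% | 52/90 = 57.8% | 52/100 = 52.0% | 52/120 = 43.3% |
| 40 | 52/100 = 52.0% | 52/110 = 47.3% | 52/120 = 43.3% | 52/140 = 37.1% |

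The overstatement factor runs from 110/100 = 1.10 to 104/64 = 1.63. The gap runs from 52.0 − 47.3 = 4.7 to 81.3 − 50.0 = 31.3 percentage points. Within each row the proportion as defined stays the same however many patients refuse the pricks or questionnaires.

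**The case against.** The best counter-argument is that the article never says these patients leave the denominator. A team could log someone who declines because of the pricks as an eligible decliner, and the detailed protocol is a supplementary file not seen here. This is fair, and it makes the harm conditional on how the definition is applied. It does not remove the point: the article fixes the denominator by eligibility and fixes eligibility by willingness, and no text shown puts these patients back.

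Four stronger readings are tempting and not supported.

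- *Only the three severity tests are checked before approach.* The Screening procedures section does not say *only*. It also omits age, diabetes and pregnancy, so it is not a full list of checks and cannot settle when willingness is judged.
- *All refusals, or all evidence on the pricks, vanish.* Refusals for other reasons stay in the denominator. Non-adherence and withdrawal after entry still lower the outcome. Physical inability to prick is ordinary eligibility.
- *The definitive trial's recruitment forecast must be too optimistic.* The article also reports the number of eligible patients. If unwilling patients drop out of both figures, eligible count times acceptance percentage still gives the same number recruited. The forecast goes wrong only if the percentage is applied to a pool defined on clinical criteria alone.
- *The bias is known to be large.* Every r and u above is assumed. Comparing confidence intervals for the two proportions would add nothing, because both have the same numerator and differ only in the denominator.

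Excluding unwilling patients from randomisation is normal and is not criticised here.

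**Conclusion.** The point holds as a flaw in the definition of the primary outcome. Read literally, the feasibility proportion is partly conditioned on the willingness it is meant to measure. It is too high by the factor (C + r + u)/(C + r) whenever any approached patient is ruled out for unwillingness.

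The direction follows from algebra. The size cannot be found from the article, and if u is zero nothing changes. The conclusion assumes that the eligibility lists are applied as written and that some unwillingness emerges at or after approach.

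This should be fixed rather than treated as fatal. The article states no progression threshold that depends on the figure, and part of the acceptability signal survives through adherence after entry.

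**What to change.** Leave the entry criteria as they are and change only the denominator:

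1. Define the primary denominator as all approached patients who meet the clinical criteria.
2. Count as non-consent any approached patient who will not finger-prick (including needle fear given as the reason to decline) or will not complete the questionnaires.
3. Keep physical inability to finger-prick as ineligibility, recorded separately from unwillingness. The current criterion combines the two.
4. Tabulate non-consent by reason from the screening log.
5. Report the proportion over eligible patients, as now worded, as supplementary.

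If the full protocol or the log already codes refusals this way, stating the definition explicitly is enough. Otherwise the cost is one reason code on the log and a less favourable headline figure. Treatment, randomisation and sample size are untouched. Recruitment is described as under way, so the code should be added promptly: reasons not recorded when a patient declines may not be recoverable later.

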### Intervention

#### Arm A—FAB plus conventional treatment

The patients will use FAB therapy alongside conventional therapy (artificial tears, ciclosporine drops or punctal plugs/cautery) as recommended by their treating ophthalmologist. Hands will be washed with soap and water, dried and then a fingertip of the hand will be wiped with an alcohol-based wipe and self-pricked using a standard diabetic lancet. The drop of blood produced as normal is applied to the lower fornix of the affected eye(s) with the lower lid pulled down slightly by the patient. The blood will be applied four times a day. A fresh finger will be used for each eye and blood wiped away with the alcohol-based wipe. Patients will be advised to keep nails short and to avoid nail varnish. The FAB intervention will be applied at least 15 min after any artificial tears and participants must not use drops for at least half an hour after this.

